## Abstract

**Background:**

Thoracic surgery appears to be the treatment of choice for many lung cancers. Nevertheless, depending on the type of surgery, the chest area may be painful for several weeks to months after surgery. This painful state has multiple physical and psychological implications, including respiratory failure, inability to clear secretions by coughing, and even anxiety and depression that have negative effects on recovery.

**Objective:**

The aim of this study is to evaluate the effect of a neurofeedback-based intervention on controlling acute post-surgery pain and improving long-term recovery in patients who undergo thoracotomy for lung resection for non-small cell lung cancer (NSCLC) at an academic oncologic hospital.

**Methods:**

This study will be based on a 2-parallel group randomized controlled trial design, intervention versus usual care, with multiple in-hospital assessments and 2 clinical, radiological, and quality of life follow-ups. Participants will be randomized to either the intervention group receiving a neurofeedback-based relaxation training and usual care, or to a control group receiving only usual care. Pain intensity is the primary outcome and will be assessed using the Numeric Pain Rating Scale (NRS) in the days following the operation. Secondary outcomes will include the effect of the intervention on hospital utilization for pain crisis, daily opioid consumption, anxiety, patient engagement, blood test and chest x-ray results, and long-term clinical, radiological, and quality of life evaluations. Outcome measures will be repeatedly taken during hospitalization, while follow-up assessments will coincide with the follow-up visits. Pain intensity will be assessed by mixed model repeated analysis. Effect sizes will be calculated as mean group differences with standard deviations.

**Results:**

We expect to have results for this study before the end of 2016.

**Conclusions:**

The proposed innovative, neurofeedback- and relaxation-based approach to support post-surgery pain management could lead to significant improvements in patient short and long-term outcomes.

##  Introduction

### Background

Lung cancer has been the most common cancer worldwide since 1985, both in terms of incidence and mortality [1-3], and it is among the top five most frequently diagnosed cancers in Italy [4]. Thoracic surgery appears to be the treatment of choice for many lung cancers. Nevertheless, depending on the type of surgery, the chest area may be painful for several weeks to months after surgery. Indeed, after a thoracotomy, patients often suffer from a persistent pain [5-7] due to the skin incision or deeper tissue injuries, costovertebral joint disruption, resection or fracture of ribs or sternum, and further irritation of the pleura by thoracostomy tubes [8,9]. This painful state has multiple implications, including respiratory failure due to limiting inspiration (because deep breathing requires stretching the incision), or an inability to clear secretions by coughing [10]. Acute pain after surgery can become chronic and persist for more than a year in 21%-67% of patients [11,12]. Moreover, a lot of clinical and demographic factors can contribute to the development of chronic postsurgical pain including psychological conditions (anxiety or depression states), previous surgery, other simultaneous pain, injuries of the chest wall, youth, female gender, and increased levels of pain and analgesic use in the perioperative period [13].

Cooley et al [14] have shown that a high level of post-operative pain in lung cancer patients may exacerbate the fear that movement or physical activity will worsen their condition. This belief can lead to catastrophic appraisals of pain sensations that promote a self-perpetuating cycle of behavioral avoidance, hypervigilance, or distress symptoms [15-18], as well as reduced social activity and global perceptions of decreased health [13]. Researchers investigating psychological aspects of persistent pain have shown that the tendency to focus on pain and to negatively evaluate one's ability to deal with pain, pain-related anxiety, fear, and helplessness are associated with increased pain, psychological distress, and physical disability [19]. Post-thoracotomy pain syndrome and its social consequences have been also investigated by a nationwide study in Denmark [20] that highlighted how partial nerve injury and general pain hyperresponsiveness influence daily activities, even 12-36 months after surgery.

These data highlight the importance of finding effective, early interventions in the presence of painful medical procedures [17,19]. Several studies have demonstrated the effectiveness of non-pharmacological techniques (eg, relaxation) that, in addition to traditional treatments, are able to significantly reduce the acute pain and distress associated with invasive medical procedures [21,22]. Patients who undergo relaxation techniques in different health care settings suffering from acute or chronic pain have been shown to experience less pain compared to those who only undergo traditional treatments [23-27]. In particular, Syrjala et al [28] conducted a study to evaluate the effectiveness of cognitive-behavioral techniques and relaxation in reducing cancer-related pain and found that patients who received these type of treatments, in addition to medical care, reported less pain than the control groups. Although further analyses are required [29], relaxation is a non-pharmacological intervention that may control pain in cancer patients [30].

Many non-pharmacological interventions and interactive new technologies, such as video games and virtual reality environments, can greatly impact pain reduction. By playing a game or being immersed in a virtual environment, users experience an attentional competition between a highly salient sensation (pain) and a consciously directed focus on some other information processing activity [31]. The consequence is a reduced pain perception [32-35], as well as observed changes at a neuroanatomical level. Hoffman et al [36,37] conducted an fMRI study to monitor the brain activity in healthy subjects receiving thermal brain stimulation and showed that virtual reality alone significantly reduced the worst pain and pain unpleasantness, as well as pain-related brain activity in the insula and thalamus. Moreover, combined opioid plus virtual reality exposure reduced pain reports more effectively than did opioid alone on all subjective pain measures [38]. These studies demonstrate that, by distracting subjects from a highly salient sensation of pain, virtual reality may change not only the psychological perception of pain, but also the neuroanatomical networks involved in its modulation [39].

Serious games and virtual realities have been used in different contexts to modulate pain perception. In a recent review, Keefe et al [40] affirmed that virtual reality-based behavioral programs can be used to reduce acute or chronic pain among patients undergoing different medical interventions and rehabilitation programs, such as burn wound care, needle-related procedures, intravenous placement, dental treatments, or postoperative pain. In addition, actively participating in distracting tasks have effects not only on concurrent pain experiences, but long term as well, such as the vividness of memories associated with a traumatic event [33], functional performance, energy level, and time of recovery [34].

Since relaxation, distraction, and new technologies have beneficial effects on pain reduction, we propose to implement a research protocol that, by merging these factors, could help post-operative lung cancer patients to cope with acute pain generated by surgery. The technology that best suits our aim is based on the brain-computer interface (BCI) method, which enables a quick measure of brain activity while providing a neurofeedback (based on simple visual or auditory stimuli, or complex virtual environments) to help the user modulate her/his brain activity to accomplish her/his intents [41]. One of the most user-friendly, simple-to-use and low-cost BCI devices on the market is produced by NeuroSky, who sell a non-invasive, dry biosensor that can read electrical activity in the brain to determine attention and relaxation states. The device, called MindWave, is a portable electro encephalogram (EEG) developed to capture neural activity using three dry electrodes (located beneath the ears and the forehead), and decode them by applying specific algorithms. The MindWave device provides information on a user’s delta, theta, alpha, beta, and gamma brainwave band power levels [42]. The power levels can be interpreted by comparing them to themselves, and with each other, to determine relative quantity and temporal fluctuations [43]. Despite that the MindWave device cannot be used to deeply and precisely monitor the EEG brain activity, it is effective in recording the level of attention and relaxation of the user through the analysis of brain wave synchronization and desynchronization [44]. Moreover, the MindWave device works with engaging applications that help users to improve their abilities to reach attentive or relaxed states by giving them specific visual and auditory feedbacks in response to their brain activity.

We believe that the MindWave and its associated applications can benefit patients in the following ways (1) train them in relaxation techniques, (2) engage them in active tasks, and (3) by receiving motivation neurofeedback, push them to continuously improve their performance. Moreover, due to its ease of use, MindWave can be used by patients the precise moments they are experiencing acute pain.

Our goal is to help patients with lung cancer post-operative acute pain gain better control of their symptoms using this innovative, neurofeedback-based pain-control strategy. We hypothesize that patients randomized to receive the intervention will have better pain outcomes, measured by pain intensity, and better medical and psychological outcomes compared with patients receiving usual care.

### Primary Aim

Our primary aim is to evaluate the effect of neurofeedback on pain control in patients with lung cancer who have been recently operated on.

### Secondary Aims

Secondary outcomes include evaluating the effects of neurofeedback on (1) hospital utilization for pain crises, (2) daily opioid consumption, (3) level of anxiety, (4) participants’ pattern of engagement with the MindWave tool, and (5) blood test and chest x-ray results. Long-term outcomes also include clinical, radiological, and quality of life evaluations at the 1 and 4 month follow-ups.

##  Methods

### Trial Design

This study is based on a 2-parallel group randomized controlled trial design (intervention vs usual care), with multiple in-hospital assessments and 2 follow-ups (at 1 and 4 months) based on clinical, radiological, and quality of life assessments. Follow-ups will coincide with the follow-up visits. The research design is shown in Figure 1.

**Figure 1 figure1:**
[figure not shown]
Schematic representation of the trial design.

### Participants

Participants included in this study will be recruited from the thoracic surgery unit of the European Institute of Oncology (IEO), Milan, Italy. To be considered eligible to participate, patients must fulfill all of the following inclusion criteria (1) they must be aged ≥18 years, (2) able to consent for self, (3) have a primary diagnosis of non- small cell lung cancer (NSCLC), and (4) they must have undergone a thoracotomy for lung resection <12 hours prior to the first pain assessment. Ineligible patients will be defined as those who (1) have any significant medical or psychiatric comorbidities (other than depression or anxiety), (2) cognitive impediments that would prevent them from being able to utilize the MindWave device, (3) have a known history of substance abuse, and (4) are simultaneously participating in any other research protocols that may have an impact on pain intensity.

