#### Randomization and Blinding

An independent researcher with no direct contact with the participants will use a computer-generated randomization with a 1:1 ratio and permutated blocks to optimize balance in each treatment arm. Due to the nature of the study, participants, care providers, and researchers cannot be blinded for the allocated treatment. However, the data analysis will be blind, as all of the patients receive a unique study code, under which their data is stored in the database.

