### Outcome Evaluation

#### Data Collection Materials

We will assess one primary outcome and several secondary outcomes. A number of validated instruments will be used to assess the outcomes at multiple time points during the hospitalization and follow-ups. The patients, both in the treatment and in the control arms, will be asked to complete them at specific time-points without the supervision of the research assistants. Hospital nurses will be asked if they completed all the outcome measures, as requested by the protocol, at the end of each day. Demographic and clinical information of each participant will be also collected.

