#### Statistical Analysis

Statistical analysis will be conducted with the SPSS Software, version 22, with an alpha of .05 set a priori for all analyses. Descriptive statistics will be used to summarize baseline demographic characteristics by study arm. Continuous variables will be compared between the two groups using a *t* test and categorical variables will be compared using a chi-square test. Pain intensity, our primary outcome, measured longitudinally, will be assessed by mixed model analysis of variance with treatment assignment as the between-group factor and time as the within-subject factor. Effect sizes will be calculated as mean group differences with standard deviations. A similar approach will be used to analyze continuous secondary outcomes while categorical outcomes will be analyzed by chi-square tests.

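### Neither the opioid-consumption outcome nor its stated model accounts for pre-admission opioid dose, which may cost precision on a secondary outcome

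*Protocol article*

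**What the plan says.** All of this is in the protocol article.

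- **Participants.** Two exclusions come near the point. One removes patients who "have a known history of substance abuse". The other removes those who "have any significant medical or psychiatric comorbidities (other than depression or anxiety"). Prescribed opioid use and chronic pain are not named in either, and the word significant is not defined.
- **Secondary Outcomes.** Opioid consumption is quantified as the daily dose converted to oral morphine equivalents. No change from a pre-admission dose, or excess over it, is mentioned.
- **Statistical Analysis.** The primary outcome is analysed by "mixed model analysis of variance with treatment assignment as the between-group factor and time as the within-subject factor". For the rest, "A similar approach will be used to analyze continuous secondary outcomes". No baseline covariate is named.
- **Randomization and Blinding.** Allocation is by "computer-generated randomization with a 1:1 ratio and permutated blocks to optimize balance in each treatment arm". No stratification factor is stated.
- **Data Collection Materials.** "Demographic and clinical information of each participant will be also collected". The items are not listed.
- **Background.** Among the contributors to chronic postsurgical pain, the authors list "other simultaneous pain, injuries of the chest wall, youth, female gender, and increased levels of pain and analgesic use in the perioperative period".

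**The concern.** Prescribed long-term opioid use is not substance abuse, so a patient taking opioids for another pain condition can enter the trial unless the comorbidity exclusion is read to cover that condition. Part of such a patient's daily dose after surgery may simply continue earlier intake, which a relaxation aid used over a five-day stay is unlikely to change. That part is roughly constant within the patient and differs between patients. In a model with only treatment and time it goes into the between-patient variance, and averaging over more hospital days does not shrink it.

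What is at stake is the precision of one secondary comparison. It is still worth protecting. Daily opioid consumption is a named secondary aim, and usual analgesia continues in both arms, so some benefit could appear as less drug rather than as a lower pain score.

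**Working it through.** The protocol's one sample-size figure, 40 per arm, was derived for pain intensity. There is no SD, target difference or share of prior users for the opioid outcome, so there is no stated figure to reproduce. Only the 40 per arm below comes from the document; the other inputs are assumptions.

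**Inputs**
- n = 40 per arm (Sample Size Estimation).
- p, the share of patients on opioids before admission: 5-20% (assumed).
- m, their pre-admission dose, carried through unchanged into the hospital total: 30-60 mg/day (assumed).
- s, the SD of daily dose among patients not on opioids before admission: 20-40 mg/day (assumed).

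**Variance factor.** If a share p carries a constant extra dose m, the added variance is p(1-p)m², and the unadjusted variance is multiplied by 1 + p(1-p)m²/s². The last column is the power of a two-sided t test at .05 with 40 per arm, for an assumed standardised effect of 0.6 (a difference of 0.6 s). Without the added variance that power is 75.5%.

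| Case | p | m | s | Added variance | Variance factor | SD factor | Power |
|---|---|---|---|---|---|---|---|
| Low end | 0.05 | 30 | 40 | 0.0475 × 900 = 42.75 | 1 + 42.75/1600 = 1.03 | 1.01 | 74.4% |
| Midpoints | 0.125 | 45 | 30 | 0.1094 × 2025 = 221.5 | 1 + 221.5/900 = 1.25 | 1.12 | 66.1% |
| High dose, low SD | 0.10 | 60 | 20 | 0.09 × 3600 = 324 | 1 + 324/400 = 1.81 | 1.35 | 50.4% |
| High end | 0.20 | 60 | 20 | 0.16 × 3600 = 576 | 1 + 576/400 = 2.44 | 1.56 | 39.6% |

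The third row is not a central case, because it pairs the highest assumed dose with the lowest assumed SD.

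**Chance imbalance.** Suppose 8 of the 80 patients are prior users (p = 0.10). With 40 per arm, a 6:2 split or worse, in either direction, has hypergeometric probability of about 26%. At 60 mg/day a 6:2 split moves the difference between arms by (6 - 2) × 60/40 = 6 mg/day. The standard error of the difference before the added variance is s√(2/40), which is 4.5 mg/day at s = 20 and 8.9 mg/day at s = 40. The shift is therefore 0.7 to 1.3 standard errors. This is the same variability as in the table, seen in a single realised allocation, and is not a second loss on top of it.

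**A single extreme patient.** One patient on 120 mg/day moves an arm mean by 120/40 = 3 mg/day, or 0.3 to 0.7 of a standard error. One such patient would not dominate the comparison.

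**The case against.** The strongest reply has four parts.

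- **Recording.** A reader might infer that the pre-admission dose goes unrecorded. The article does not say so. Clinical information is collected without an item list, and a condensed article normally leaves that list to the full protocol. This objection stands, and the point is confined to what the outcome definition and stated model do with the dose.
- **Eligibility.** A reader might also infer that every long-term opioid user qualifies. The comorbidity exclusion could remove some of them. This also stands, but only in part: with the term undefined and chronic pain unnamed, nothing shows that it removes them all.
- **Place of the fix.** Covariates for a secondary outcome are commonly left to the analysis plan, and a similar approach does not forbid them. This limits the point to an improvement. It does not dispose of it, because the model that the article does state has two factors and no baseline term.
- **No bias.** Allocation is 1:1, so prior intake is balanced in expectation. This is correct. Reading the gap as a systematic distortion of the treatment effect would be wrong.

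The Background list is weak support as well. It concerns chronic postsurgical pain, and perioperative analgesic use is not the same as opioid use before admission. It shows that the authors regard concurrent pain and analgesic use as relevant, and no more. Likewise, the Discussion presents less analgesic use as something that could follow from positive results, not as an expected finding.

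**Conclusion.** The point holds as a modest loss of efficiency on a secondary outcome. The printed criteria do not name prescribed opioid use, and neither the outcome nor its stated model takes account of the dose before admission. The consequence is extra between-patient variance and possible chance imbalance at 40 per arm, without systematic bias.

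The size is unknown from the document. Under the assumed ranges it runs from negligible (variance factor 1.03) to substantial (2.44), and the midpoints imply an SD about 12% larger. All of these results assume that pre-admission intake adds fully to the in-hospital dose. If it is partly replaced by the postoperative regimen, the loss is smaller. The primary pain comparison is outside this point.

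**What to change.** Keep eligibility unchanged. Patients are screened after admission and before randomisation (Recruitment Procedure), so make sure that the pre-admission opioid dose, in oral morphine equivalents per day, is recorded then in both arms, if it is not already among the clinical data collected. Recording it before allocation matters because patients, care providers and researchers are unblinded afterwards. Then state that this dose is a covariate in the opioid-consumption model, alongside treatment and time.

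The cost is at most one extra data field and one model term. If the dose is already collected, only the model term is new. The gain will be small if few patients use opioids before admission.

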### Recruitment Procedure

All patients who are planned to undergo a thoracotomy for lung resection at the European Institute of Oncology, thoracic surgery unit, are considered potential candidates for the present study. Once admitted in the hospital, they will be screened by a trained research assistant to verify their eligibility. Eligible patients will be asked to sign the informed consent, and then randomly assigned to the intervention or control groups. All participants will be instructed to continue to receive medical care from physicians as usual. Subjects included in the intervention arm will be trained on the use of the technology and relaxation technique prior to the operation by a research assistant. They will also receive a MindSet device and tablet with the app Focus Pocus installed on it, for the entire duration of hospitalization (5 days).

### Intervention

#### Framework for Intervention

This neurofeedback-based pain-management program is based on the hypothesis that a relaxation training that provides users an immediate feedback on their performance, as well as a playful environment that moves the patient’s focus from the painful sensation to a specific task can be effective in reducing acute pain perception. In fact, the use of engaging and fun mini-games encourages patients to exercise important psychological processes that underlie their ability to control their own brain responses and, consequently, their behavior.

#### Hardware and Software Equipment

Powered by NeuroSky’s Brainwave Technology, the Mindwave headset is a slim, plastic device which fits comfortably, if not unobtrusively, over the user’s left ear (see Figure 2). The Mindwave mobile device uses a single sensor positioned on the forehead to allow users to view their brainwaves in real-time. The Mindwave headset picks up the brain’s electrical activity and divides the signal by frequency into various types of waves, allowing it to infer how relaxed (as measured by alpha and theta waves) or concentrated (as measured by beta and gamma waves) users are. In order to allow the headset to filter out non-brain related electrical activity, a ‘reference’ contact, in the form of a clip that attaches to the earlobe, is included. The MindWave mobile device can connect, via bluetooth, to different devices, and works with most modern operating systems (Windows X or newer, Mac OS X 10.6.5 or newer) and mobile devices running Android or iOS. Its battery life is rated at 8-10 hours with a single AAA battery. Although it will take a minute or two to adjust the headset the first time the user puts it on, setup is relatively simple.

The MindWave mobile costs approximately 100 euros (€) and comes bundled with many free and paid applications, but we limited our choice to those available for the iPad tablet specifically as it is one of the most confortable devices (in terms of portability, weight, and usability) that can be used by bedridden patients. After having tested all the existing iOS-based apps, we opted for the one called “Focus Pocus-BrainControl”. Focus Pocus is a mix of mini-games that uses live brain electrical activity (ie, EEG) from the NeuroSky MindWave device to alter the circumstances of the player. What happens in the game depends on how relaxed the player is. Focus Pocus attracted our attention for the following reasons (1) ease of use, and has a very high-quality interface, yet is low in cost, (2) the games are engaging and fun with a unifying theme, (3) provides cognitive exercises designed by qualified experts, (4) can be used anywhere and anytime without specific supervision, (5) has been already used for scientific purposes [45,46], (6) designed to provide an environment to practice the relaxation skill (other than attention, impulse-control, and memory), (7) can register the user’s training performance in terms of time of use and achievements, and (8) rewards the users’ progress by providing them behavior ratings at the end of each trial. With respect to relaxation, for example, in the Focus Pocus BrainControl games, the outcome of any relaxing experience is the result of the content presented, the environment in which it is presented, and the person’s readiness to learn. This readiness depends on relaxation (a “state” factor) as well as being able to control impulses and ignore internal (into the game) and external (pain sensation) distractions. In order to guarantee improvement in performance, the difficulty levels of the games are adaptive, and can be adjusted on a per game basis to the performance of the users.

A screenshot of one of the of the Focus Pocus games is shown in Figure 3. A single electrode on the Neurosky headset (placed on the forehead) is able to pick up a few simple and characteristic brainwaves (created by activity in populations of neurons), some that have been shown to be enriched when the subject is awake and attentive (eg, beta waves), and some when the subject is relaxed (eg, alpha waves). Neurosky has developed algorithms to funnel these and other brain waves into measures of “focus” and “meditation.” In particular, in this game, the player needs to attain a certain level of meditation to win a duel with an evil necromancer. The idea is that through these different activities, the players would be exercising mental capacities that would generalize outside the game (when they experience acute pain, for example).

For the present protocol, 2 provided tablets and MindWave mobile devices will be used at the same time on 2 different patients. They will be given to the patients the day before the operation and left at subjects' bedside for the duration of their hospital stay. The nurses and the patients will be asked to take care of the devices. The MindSet device and its sensor contact points will be cleaned regularly with an alcohol-based cleaner and a soft cloth included in the MindSet casing to prevent cross-infection and to guarantee good signal quality.

